#### Interviews

We will conduct semi-structured KI interviews (*N* = 300) at end-of-intervention and 6 months post-intervention to obtain supplemental data about organizational changes for evidence-based CVD prevention (implementation policies and practices) and influential inner and outer context events. The KI interview at end-of-intervention will also ask about acceptability of the implementation support received (implementation effectiveness). The KI interview 6 months post-intervention will ask about practice-level outcomes (innovation effectiveness).

#### EHR/informatics

We will obtain performance data on the ABCS measures (implementation effectiveness) and patients’ intermediate clinical outcomes (innovation effectiveness) from the EHR. The ABCS measures and clinical outcomes will be collected at baseline, during the intervention (quarterly), at the end of the intervention, and post-intervention (6 and 12 months follow-up). The EHR will also supply race/demographic data. EHR data will be routed to the CCNC Informatics Center, where the data will be extracted, normalized, and placed in a standard report used for the evaluation and sent back to the practices.

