### Research design

HHN is a stepped wedge, stratified, cluster randomized trial. Each practice will start the trial as a control, receive the primary care practice support intervention at a randomized time point, and then enter a maintenance period 12 months after the start of the intervention. The intervention will be randomized to practices in one of four strata defined by region of the state (east or west) and degree of practice readiness for change (described below). Specifically, 75 practices in each region with a high degree of readiness will be randomized 1:1:1 in blocks of 3 prior to month 8 to receive the intervention at month 9, 11, or 12. An additional 75 practices within each region that have a low degree of readiness or are recruited later will be randomized 1:1 in blocks of 2 prior to month 13 to receive the intervention at month 14 or 16. The sites will be ordered within each stratum based on time of enrollment with the blocking based on this ordering. The study’s statistician will generate the stratified permuted-block random allocation lists using a computer program. As practices are enrolled, the project management system will use the randomization schedule to randomize practices and assign their intervention start date. A practice is considered randomized once an intervention start date has been assigned. Neither study personnel nor participating practices will be blind to randomized start dates.

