#### Statistical analysis

The statistical analysis of the primary outcomes for Aim 1 will be based on a generalized linear mixed model (GLMM) for longitudinal binomial data at the practice level. Allowing for the number of patients who are observed within a practice to vary across time, the models will be estimated by maximizing the pseudo-likelihood, specifying practices as clusters, and using empirical variance estimators. For example, the number of hypertensive patients whose blood pressure is under control *Y*_it_, out of *N*_it_ hypertensive patients, will follow a binomial (*N*_it_, *π*_it_) distribution where, conditional upon a practice-specific random intercept *b*_i0_ and slope *b*_i1_, π_it_ = *E*(*Y*_it_/*N*_it_|*b*_i0_,*b*_i1_) is the expected proportion of hypertensive patients whose blood pressure is controlled within the *i*-th practice in the *t*-th month; *t* = s_i_ (baseline), s_i_ + 3, s_i_ + 6, s_i_ +9, s_i_ + 12, s_i_ + 18 (6 month post-intervention follow-up), and for some practices s_i_ + 24 (12 month post-intervention follow-up). The GLMM is1$$ \mathrm{Logit}\left({\uppi}_{\mathrm{i}\mathrm{t}}\right) = {\beta}_0 + {b}_{\mathrm{i}0} + {\beta}_1{X}_{\mathrm{i}1} + {\beta}_2{X}_{\mathrm{i}2} + {\beta}_{12}{X}_{\mathrm{i}1}{X}_{\mathrm{i}2} + {g}_1\left({t}^{*};\uppsi \right) + {b}_{\mathrm{i}1}t + {g}_2\left(t;\uplambda \right){X}_{\mathrm{i}\mathrm{t}3} + {g}_3\left(t;\uptheta \right){X}_{\mathrm{i}\mathrm{t}4} $$where *X*_i1_ = 1 indicates east region and 0 for west region; *X*_i2_ = 1 indicates higher readiness and 0 for lower readiness stratum; *g*_t_(*t*^*^;ψ) is a smooth spline function of calendar time (*t*^*^) for the secular trend corresponding to the control condition with finite dimensional parameter ψ; *X*_it3_ = 1 indicates the active (12 months) intervention period versus 0 otherwise and *g*_2_(*t*; λ) is function for four piecewise conjoined linear segments each of 3 months duration with λ being the vector of slope parameters; *X*_it4_ = 1 is an indicator for the maintenance period versus 0 otherwise and *g*_3_(*t*;θ) is a function for two piecewise conjoined linear segments the first of 6 months duration to which all practices will contribute data and the second 6 months durations to which only a subset of practices will contribute data as determined by the stepped-wedge design. Finally, *b*_i0_ and *b*_i1_ are assumed to be bivariately normal random variables with respective variances *σ*_0_^2^ and *σ*_1_^2^ and covariance *σ*_01_. Primary interest is in the treatment effect describing the log odds of a randomly sampled patient in a practice having the outcome 12 months post-intervention relative to the log odds of a randomly sampled patient from the same practice having the outcome during the pre-intervention period; this log odds ratio is well-defined as a function of λ parameters. Finally, the average causal effect of 12 months of intervention will be calculated as the average difference in proportions, Σ_i_[E(*Y*_it_/*N*_it_|*b*_i0_,*b*_i1_,*t* = s_i_ + 12)—E(*Y*_it_/*N*_it_|*b*_i0_,*b*_i1_*t* = s_i_)]/300; a 95 % confidence interval will be determined by bootstrapping. The random coefficients logistic model (1) will be fitted using SAS Proc GLIMMIX.

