#### Statistical power

Power to detect the effect of intervention after 12 months with respect to the outcome of hypertension control is simulated for the stepped-wedge study design assuming 300 practices, and an average of *μ* = 1200 or 1600 patients per practice (assuming a typical practice has 4 physicians with 300 or 400 patients per physician). For data collection months *t* = s_i_ (baseline), *s*_i_ + 3, *s*_i_ + 6, *s*_i_ +9, *s*_i_ + 12, and *s*_i_ + 18 (6 months post-intervention follow-up), power calculations are based on practice-month summaries consisting of 1800 binomial observations (6 × 300). Power is determined by simulating data from a model similar to model (1) but, for simplicity, assuming no temporal trend:2$$ \mathrm{logit}\left\{E\left({Y}_{\mathrm{i}\mathrm{t}}/{N}_{\mathrm{i}\mathrm{t}}\Big|{b}_{\mathrm{i}0},{b}_{\mathrm{i}1}\right)\right\} = {\beta}_0 + {b}_{\mathrm{i}0} + {\beta}_2{X}_{\mathrm{i}2} + {\beta}_3{X}_{\mathrm{i}\mathrm{t}3} + {b}_{\mathrm{i}1}t $$where *X*_it3_ = 0 if *t* = s_i_; *X*_it3_ = (*t* – s_i_)/12 for *s*_i_ < *t* ≤ *s*_i_ + 12, and *X*_it3_ = 1 for *t* = *s*_i_ + 18. This model assumes a linear logistic trend during the active intervention period and a constant slope during the maintenance period equal to the 12-month intervention effect. Additionally, model (2) specifies a practice-specific intercept and slope assumed to be normally distributed with means 0 and variances *σ*_0_^2^ = 0.42, *σ*_1_^2^ = 0.32 and covariance *σ*_01_ = −0.15, values estimated from preliminary pretest-posttest data on 19 medical practices (not shown). Primary interest is in exp(*β*_3_), the practice-specific odds ratio of having a positive outcome (e.g., blood pressure controlled) after 12 months intervention relative to baseline. The number of patients in the i-th practice assumed to be constant across time (*N*_i_ = *N*_it_ for all *t*) was randomly selected from *N*_i_ ~ *N*(*μ*, *μ*^7/4^) to account for expected variability in practice size. A complete data set is then generated using model (2) with (*β*_0_ = 0.50, *β*_2_ = 0.05, *β*_3_ = 0.05) corresponding to a baseline of 62 % blood pressure control for least ready practices. The fraction of times that *H*_0_: *β*_3_ = 0 is rejected with two-sided *α* = 0.05 Wald tests under the correctly specified model was taken to be the simulated power for detecting a non-null odds ratio *β*_3_. When the true *β*_3_ = 0, the results represent simulated type I error, which is seen to be close to the nominal 0.05 significance level. The stepped-wedge design has excellent power for the outcome, percentage of hypertensive patients with controlled blood pressure (see Additional file 1).

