### Limitations

Recruiting and retaining a large number of practices to engage in a yearlong, comprehensive quality improvement effort poses significant challenges. Potential recruitment barriers include fear of financial risk, reluctance to share data, acquisition by larger health systems, and competing priorities. Potential retention barriers include loss of a key clinician, resignation of a practice manager, and financial difficulties. We will attempt to mitigate these barriers by using practice facilitation to help practice achieve other goals (e.g., PCMH recognition) or enhance billing for services. Also, CCNC and AHEC will leverage their strong relationships with hospitals and health systems to boost recruitment and prevent attrition.

Our stepped-wedge study design affords some control of the effects of secular trends and other factors unrelated to our comprehensive quality improvement strategy. We will supplement this by documenting and including in our statistical analysis temporal events that could affect the implementation and outcomes of the strategy. However, the effects of outer context factors can be challenging to measure and model.

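### One control reading per practice, and all practices crossed over by month 16: the 12-month effect has no concurrent control and its secular-trend adjustment is very imprecise

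*Protocol article*

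**What the plan says.** All references are to the protocol article.

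- **Research design.** High-readiness practices are "randomized 1:1:1 in blocks of 3 prior to month 8 to receive the intervention at month 9, 11, or 12". Practices with low readiness, or recruited later, are "randomized 1:1 in blocks of 2 prior to month 13 to receive the intervention at month 14 or 16". There are 75 practices in each of four region-by-readiness strata.
- **EHR/informatics.** "The ABCS measures and clinical outcomes will be collected at baseline, during the intervention (quarterly), at the end of the intervention, and post-intervention". Table 1 gives the same timing codes for the ABCS measures.
- **Aim 1, Statistical analysis.** The analysis times for model (1) run from the practice's own start, s_i, through +3, +6, +9, +12 and +18 months (+24 for some). Only s_i precedes the intervention. A calendar-time spline, g1, represents the control-condition trend. The intervention effect has four free linear segments of 3 months each. The primary contrast compares 12 months after start with the pre-intervention period.
- **Aim 1, Statistical power.** Six readings on 300 practices are used, with the secular trend left out for simplicity.
- **Aim 2.** Surveys are taken at s_i and s_i + 12 only. Model (3) includes g1, and the result is described as an average causal effect adjusted for secular trends.
- **Limitations.** "Our stepped-wedge study design affords some control of the effects of secular trends and other factors".

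**The concern.** A stepped-wedge design controls for secular change because, at a given calendar time, some randomized clusters are treated and others are not. That needs outcome readings on a shared calendar while some clusters still wait. Here readings are tied to each practice's own start, so a waiting practice contributes nothing until the month it begins.

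Blood pressure control, statin use and tobacco screening could all drift over a year without this intervention. If the drift cannot be separated from the effect with useful precision, there are two outcomes. A model that includes the trend gives an interval too wide to inform. A model that omits it gives an uncontrolled before-after change.

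**Working it through.** **1. Calendar of readings** (start months from Research design, reading times from model (1))

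| Start | Practices | Control reading | +3 | +12 |
|---|---|---|---|---|
| 9 | 50 | 9 | 12 | 21 |
| 11 | 50 | 11 | 14 | 23 |
| 12 | 50 | 12 | 15 | 24 |
| 14 | 75 | 14 | 17 | 26 |
| 16 | 75 | 16 | 19 | 28 |

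The 12-month readings come 5 (21 − 16) to 12 (28 − 16) months after the last control reading. The only treated-versus-control comparison in the same month and the same randomized stratum is at month 12: month-9 starters at +3 against month-12 starters at baseline. The later strata have none.

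**2. The plan's own figures.** 6 × 300 = 1800 observations reproduces. The inverse logit of 0.50 is 62.2 %, as stated. Generalized least squares (GLS) under model (2) gives a standard error of 0.0111 and 99.4 % power at β3 = 0.05, consistent with the claim of excellent power (the table itself is in an additional file).

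**3. Inputs for the check.** Variances 0.42 and 0.32 and covariance −0.15 (Aim 1, Statistical power); binomial variance 1/(N·p·(1 − p)) with p = 0.62. Assumptions: N = 1200, the lower of the plan's two values (1600 changes nothing material), and a random slope per year, since no time unit is given. The effect is free at each reading, as in model (1), with adjustment for readiness.

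**4. Closed form.** Within a practice, calendar time = s_i + time since start, so a linear trend is identified only by differences in s_i between practices.
- High readiness (mean 10.67): 50 × (2.78 + 0.11 + 1.78) = 233.3.
- Later strata (mean 15): 150 × 1 = 150.
- Within-stratum sum of squares: 383.3.
- Intercept variance left after using the slope covariance: 0.42 − 0.15²/0.32 = 0.35.
- Standard error of 12 months of trend: 12 × √(0.35/383.3) = 0.36.

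**5. Full GLS, standard error of the 12-month log odds ratio**

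| Model | SE |
|---|---|
| Free effect, no trend | 0.033 |
| Free effect, linear trend | 0.364 |
| Free effect, quadratic trend | 0.365 |
| Linear trend, no readiness adjustment | 0.171 |
| Linear trend, random slope per month | 0.534 |

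The difference detectable with 80 % power at 62 % moves from about 2 to about 20 percentage points. Power for a 4-point gain falls from 99.9 % to 7.5 %.

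**6. Aim 2 surveys** (N = 200 per practice per time). Baselines fall at months 9–16 and end readings at months 21–28, so they never overlap. With a linear trend the SE rises from 0.036 to 0.372 (80 % baseline) and from 0.035 to 0.370 (30 % baseline). Power for the stated 0.04 difference falls from above 99.9 % to 11 %, and from 99.95 % to 8 %.

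**7. Adding control readings for practices not yet started** (Aim 1, free effect)

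| Months added | Trend | Practice slopes begin at start | Slopes run unchanged from before start |
|---|---|---|---|
| 9, 11, 12, 14 | linear | 0.036 | 0.015 |
| 9, 11, 12, 14 | quadratic | 0.059 | 0.074 |
| also 3 and 6 | linear | 0.034 | 0.008 |
| also 3 and 6 | quadratic | 0.041 | 0.032 |

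If slopes begin at start, the floor is √(0.32/300) = 0.033, because pre-start readings say nothing about those slopes.

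**The case against.** **Is the 12-month effect pure extrapolation?** A reader might infer this from the absence of controls after month 16. The document does not support it. Model (1) makes the effect a function of time since start, so treated practices at different exposures also inform the trend after month 16. Allowing the trend to bend at month 16 leaves the SE at 0.364. The weakness is that the slope is identified only between practices, and only if the effect curve is common.

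**Is secular-trend control absent?** No. Limitations claims only some control, adds that temporal events will enter the analysis, and concedes that outer-context effects are hard to model. Short exposures have a little concurrent control.

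**Does the trend alone destroy the stated power?** Not in model (2) as written. Adding a linear trend there leaves the SE at 0.0115, because the effect is forced to be linear to 12 months and then flat. Model (1) imposes no such shape, so the power section removes the problem through two simplifications together.

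**Would extra readings bring the SE to 0.015 or 0.008?** Only if each practice's slope runs unchanged from before start. The slope variance was estimated from pretest-posttest data on 19 practices, which need not describe drift under control. In addition, Table 3 defines several measures over 12 or 24 months, so readings a few months apart share patients and look-back. The calculation treats them as independent, so the real gain is smaller. The overlap also dilutes the month-12 comparison.

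**What remains of the case against.** Extra pre-start readings improve precision but create no concurrent control at months 21–28.

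**Conclusion.** The concern holds as one of precision and identification. The article gives the same schedule in its data-collection, analysis and power sections: one control reading per practice and none after month 16. Under model (1) with a linear trend, the SE of the primary 12-month log odds ratio is about 0.36, roughly 11 times the no-trend value of 0.033. The β3 of 0.05 used for power is far below it. The Aim 2 survey outcomes are affected to the same degree (about 0.036 to 0.37).

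The figures assume N = 1200, a random slope per year and readiness adjustment. Without that adjustment the SE is 0.17, but start month is randomized only within readiness strata and model (1) includes readiness. With the slope per month it is 0.53, but then the no-trend SE is already 0.39 and the stated power would not follow, so the per-year reading fits the plan better.

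**What to change.** 1. Extract ABCS counts on a common calendar for every practice not yet started: at step months 9, 11, 12 and 14, and at about months 3 and 6. Where a practice was not yet enrolled, which is possible in the strata that include later recruits, take the counts retrospectively from date-stamped records. Use all of them in model (1). Expect an SE of about 0.034–0.036 with a linear trend if practice slopes begin at start (0.04–0.06 with a quadratic trend), less the loss from overlapping look-back windows.
2. State that the 12-month effect has no concurrent control, and that its trend adjustment depends on the modelled trend and on a common effect curve by time since start.
3. Restate power with g1 and model (1)'s free effect included, and give the time unit of the random slope.
4. Report the Aim 2 survey outcomes as an adjusted before-after change, not as a causal effect; EHR extraction cannot supply the missing survey controls.

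The cost is extra runs of an extraction that the informatics center already performs, and data agreements that cover the earlier dates. Randomization, visits and staffing are unchanged.

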#### Patient surveys

We will survey 200 consecutive adult patients in each practice at baseline and at the end of the intervention to obtain patient experience data on communication and shared decision-making (innovation effectiveness). Data will be collected during an office visit using paper-based surveys. Eligible patients must have one or more of the following comorbidities: hypertension/high blood pressure, myocardial infarction/heart attack, angina/coronary heart disease, stroke, smoking, diabetes, and high cholesterol.

#### Claims data

We will use claims data at baseline, end-of-intervention, and 6 months post-intervention to assess hospitalizations for cardiovascular-related conditions, in-hospital deaths, and mortality for patients seen at participating practices (innovation effectiveness). We will have access to claims data on 85 % of the insured population in NC, specifically those covered by Blue Cross Blue Shield of North Carolina, the State Employee Health Plan, Medicare, and Medicaid. Outcomes will be aggregated to the practice level. For the baseline period, we will examine claims data for the year prior to the intervention. Following the intervention, we will examine available claims during and after the intervention for each practice.

## Measures

*Implementation support*. We will measure primary care practice support intensity as the percentage of contacts with a practice that are in-person. We will also report the actual number of in-person contacts and number of total contacts to account for variability in contacts across practices. We will also track frequency, mode, and duration of contact with academic detailers, as well as number and type of staff per practice attending collaborative meetings.

*Practice capacity for QI* encompasses two constructs. The first construct, change process capability, refers to a “state of preparedness for change that is influenced by the organization’s previous history of change, its plans for continuous organizational refinement, and its ability through its social and technical systems to initiate and sustain that change” ([10], p. 193). We will measure this construct using the Change Process Capacity Questionnaire (CPCQ) [10]. The second construct, adaptive reserve, refers to “the practice relationship infrastructure; alignment of management functions in which clinical care, practice operations, and financial functions and reflect a consistent vision; facilitative leadership; teamwork; sense-making; a positive work environment; and a culture of learning”([11], p. S37). We will measure this construct using the Practice Adaptive Reserve scale [11, 12].

*Organizational readiness for change* refers to the extent to which organizational members are psychologically and behaviorally prepared to implement change [6, 7, 13]. We will measure readiness using the Organizational Readiness for Implementing Change scale [13].

*Implementation policies and practices* are the strategies that an organization puts into place to support innovation use [9, 14]. We will measure implementation policies and practices using the Key Drivers of Implementation Scales (KDIS) [15]. PFs will rate the extent of practice implementation of the four key drivers using a 5-point, behaviorally-anchored scale. Table 2 offers an example of the KDIS for planned care.

**Table 2 Tab2:** Key Drivers of Implementation Scale (KDIS) for standardized care processes

Level	Description
0 - No activity	No activity on standardization.
1 - Protocols identified	Practice identifies sample protocols and customizes them for their practice.
2 - Staff enabled	Practice enables staff to perform roles (via standing orders, etc.) needed to implement protocols.
3 - Testing workflow	Practice is develops/tests workflows to support protocols.
4 - Implementation	Practice implements and follows at least one protocol.
5 - Full implementation	Practice monitors the system to ensure that protocols are used consistently.

*Implementation climate* refers to organizational members’ “shared summary perception of the extent to which their use of a specific innovation is rewarded, supported, and expected within their organization” ([16], p. 1060). We will measure implementation climate using a 6-item scale [17].

*Implementation effectiveness* refers to the consistency and quality of aggregate or pooled innovation use (e.g., evidence-based CVD prevention) [14]. We will assess implementation effectiveness using nine ABCS measures (see Table 3).

**Table 3 Tab3:** Process of care measures for ABCS

Ischemic vascular disease (IVD): use of aspirin or another antithrombotic	Percentage of patients aged 18 years and older with ischemic vascular disease (IVD) with documented use of aspirin or other antithrombotic.
Aspirin for the primary prevention of cardiovascular disease	Percentage of patients between the ages of 50 and 75 with an ASCVD risk score of ≥10 % who do not currently have ischemic vascular disease with documented aspirin use.
Blood pressure management: controlling high blood pressure	Percentage of patients aged 18 through 85 years of age with a diagnosis of hypertension (HTN) whose blood pressure (BP) was adequately controlled (<140/90) during the measurement year.
Blood pressure management: controlling high blood pressure	Percentage of patients aged 18 through 85 years of age with a diagnosis of HTN whose blood pressure was adequately controlled ( age 18–59 and/or people with diabetes or chronic kidney disease <140/90; age 60–85 < 150/90 ) during measurement year.
Statin therapy for prevention and treatment of cardiovascular disease	Percentage of the following patients—all considered at high risk of cardiovascular events—who were prescribed or were on statin therapy: adults ages ≥21 years who were previously diagnosed with or currently have an active diagnosis of clinical atherosclerotic cardiovascular disease (ASCVD); or adults ages ≥21 years with a fasting or direct low-density lipoprotein cholesterol (LDL-C) level ≥190 mg/dL; or adults ages 40–75 years with a diagnosis of diabetes with a fasting or direct LDL-C level of 70–189 mg/dL.
Risk-based statin therapy	Percentage of patients aged 40 through 79 years of age whose Calculated Risk Score is 10 % or greater and are on a statin.
Assessment of cardiovascular risk	Percentage of patients ages 40–79, with no evidence of prior cardiovascular event, who have documentation of required elements for cardiovascular risk assessment.
Tobacco use screening	Percentage of patients aged 18 years or older who were seen for at least 2 office visits within 12 months and who were queried about tobacco use one or more times within 24 months PQRS 226 Part A (modified).
Smoking cessation support	Percentage of patients aged 18 years and older identified as tobacco users within the past 24 months and seen for at least 2 office visits within 12 months who received cessation intervention within 24 months PQRS 226 Part B (modified).

The ischemic vascular disease use of aspirin, blood pressure management 1, tobacco use screening, and smoking cessation support measures are PQRS measures with defined measure specifications [27]. The aspirin for primary prevention, blood pressure management 2, statin for primary prevention, risk-based statin therapy, and cardiovascular risk assessment measures reflect newer evidence-based guidelines

We will measure acceptability of primary care practice support qualitatively by asking about KIs’ satisfaction with the frequency, duration, and quality of implementation support.

*Innovation effectiveness* refers to the benefits that result from innovation use (e.g., patient and practice outcomes) [14]. To capture patients’ assessment of communication, we will use selected items from the CAHPS clinician and group survey (see Table 4) [18].

**Table 4 Tab4:** Communication questions

In the last 12 months, how often did your provider		Response options
Q14	explain things in a way that was easy to understand?	•Never
Q15	listen carefully to you?	•Sometimes
Q17	give you easy to understand information about any health questions or concerns?	•Usually
Q18	seem to know about your medical history?	•Always
Q19	show respect for what you had to say?	
Q20	spend enough time with you?	

Items from the Consumer Assessment of Healthcare Providers and Systems (CAHPS) Clinician and Group Survey [18]

To capture patients’ assessment of shared decision-making, we will use selected items from the CAHPS patient-centered medical home supplement [19] (see Table 5).

**Table 5 Tab5:** Shared decision-making questions

In the last 12 months, did you and your provider talk about starting or stopping a prescription medication? If yes, complete the rest of the questions.		Response options
PCMH7	When you talked about starting or stopping a prescription medicine, how much did your provider talk about the reasons you might want to take a medicine?	Not at all, a little, some, a lot
PCMH8	When you talked about starting or stopping a prescription medicine, how much did your provider talk about the reasons you might NOT want to take the medicine?	Not at all, a little, some, a lot
PCMH9	When you talked about starting or stopping a prescription medicine, did your provider ask you what you thought was best for you?	Yes, no

Items from Consumer Assessment of Healthcare Providers and Systems (CAHPS) patient-centered medical home supplement [19]

In addition, we will assess patients’ healthcare utilization and mortality using claims data. We will measure hospitalizations for stroke, acute myocardial infarction, and angina identified via primary diagnoses and in-hospital mortality for these conditions. For patients covered by Medicare and Medicaid, we will also be able to assess non-hospital related mortality. We will also collect clinical data on patients’ blood pressure, cholesterol levels, smoking status, and CVD risk based on the ASCVD risk calculator developed by the American Cardiology Foundation and the American Heart Association (see Table 6). These clinical data will be extracted and summarized by the CCNC Informatics Center.

**Table 6 Tab6:** Practice-level patient outcomes

Outcome	Measure
Communication	Percentage of patients who answered “always” to all 6 communication questions
Shared decision-making (SDM)	Percentage of patients who answered “a lot” and “yes” to all 3 SDM questions.
Hospitalizations	Percentage of patients hospitalized for stroke, MI, angina.
In-hospital mortality	Percentage of patients hospitalized for stroke, MI, angina who died in the hospital.
Blood pressure	Percentage of patients with BP <140/90, <140/90 if 18–59 years, <150/90 if 60–85 years.
Systolic blood pressure	Percentage of patients with a SBP <140; mean (SD), median (IQR) SBP
Diastolic blood Pressure	Percentage of patients with DBP < 90; mean (SD), median (IQR) DBP
Low-density lipoprotein (LDL) level	Percentage of patients with LDL levels in the following categories: <100 mg/dL; 100 to <160 mg/dL; 160 mg/dL or more
10-year CVD Risk^a^	Mean (SD), median (IQR) of individuals who had CVD risk calculated

^a^based on ACSVD

We will measure practice outcomes qualitatively by asking whether evidence-based CVD prevention improved the practice’s standing in a pay-for-performance program, provided them with maintenance of certification credits, improved their payments through the BCBS of NC sponsored Blue Quality Physicians Program, or made them more attractive for recruitment into ACOs/Shared Savings Programs and other global payment programs.

*Inner context* refers to structural, political, and cultural features of the practice that are directly related to experiences of patients and staff, as well as features of the larger organization (if any) with which a practice is associated [20]. We will capture inner context through our measures of practice capacity for QI, organizational readiness, and implementation climate. In addition, we will assess other structural features, such as practice type (see Table 7).

**Table 7 Tab7:** Inner context measures

Practice type	Solo, single-specialty, multispecialty (NAMCS-EMR Q11-13)
Degree of integration	Practice owned by physician/group, HMO, CHC, AMC, other hospital, other corp. (NAMCS-EMR Q22)
Practice size	Number of physicians (NAMCS-EMR Q12)
Practice staffing	Number of mid-level providers (NAMCS-EMR Q14)
Patient volume	Number of office visits in a normal week (NAMCS-EMR Q10)/per provider full time equivalent (FTE)
Payer mix	Percent patient care revenue from Medicare, Medicaid, private insurance, other (NAMCS-EMR Q23)
EMR capabilities	Number and use of computerized capabilities (NAMCS-EMR Q18a-Q18j)

Items from the 2010 National Ambulatory Medical Care Survey electronic medical records

*Outer context* refers to features of the economic, political, and social context within which an organization resides [20]. Through the KI survey, we will assess the perceived influence of external events using a 3-point Likert scale (no influence to significant influence). In KI interviews, we will explore qualitatively how events rated “2” (some influence) influenced the practice’s efforts to implement evidence-based CVD prevention processes of care.

